[figure not shown]

## **Summary KWF project “The Tissue Issue”**

### **Background**

Human samples obtained during standard clinical care, such as tissue from surgery or blood, are being increasingly collected, banked and used in basic, translational and clinical research. This tissue is referred to as *residual* tissue, as compared to (extra) tissue *specifically* collected for scientific research. There is currently no standard procedure in the Netherlands that prescribes whether and how patients should be asked consent for the use of residual tissue. Empirical data about patients’ preferences and wishes regarding information and consent procedures for such use is scarce, and the available research results have not been translated to clinical practice.

### **Study objectives**

This KWF-funded project aims to determine patient preferences for and satisfaction with consent procedures regarding the use of residual tissue for research; to provide insight into the type of information patients need to decide on the use of their material in research; and to determine the feasibility of the timing and content of these procedures in clinical practice. We will compare three consent procedures with respect to several study outcomes: consent rates, and patients’ and medical staff’s satisfaction with and preferences for these procedures.

### **Methods**

In this multicentre, randomized controlled trial, 1800 patients will be recruited from four hospitals in the Netherlands (expected response rate 75%). Patients will be randomized to three study arms. In the ‘informed consent’ and ‘opt-out plus’ arms, patients are informed about residual tissue use both verbally and through a specific leaflet. These leaflets contain a consent form and an opt-out form respectively. In the third arm, the control group, no (extra) information about residual tissue use is offered, and patients may opt-out of the use of their residual tissue verbally or written. Patients to be included will be stratified by hospital and condition. Two academic and two regional hospitals will be included. Inclusion of both categories of hospitals and of patients with malignant and non-malignant diseases will increase the generalizability of the study results.

Six weeks after the intervention, patients will receive a questionnaire addressing satisfaction with and preference for the consent procedures. One quarter of the respondents will be interviewed about these topics through a semi-structured telephone interview. Six months after the intervention, respondents will receive a second questionnaire to examine whether those who made a decision about the use of their residual tissue are still aware of that decision and, if they are, whether they are still satisfied with it.

Clinicians and nurses who will carry out the interventions will receive a pre- and post-experimental questionnaire to examine their opinions about and experiences with the consent procedures.

**Results/relevance**

Expected result of this study will be an information procedure that is in accordance with patients' wishes and research needs and which can be uniformly applied in all Dutch hospitals. This will contribute to the debate about the improvement of regulations (by law or self-regulation) regarding the use of residual tissue for research.

## Introduction

### Use of (residual) human materials in research

Human samples obtained during standard clinical care, such as tissue from surgery or blood, are being increasingly collected, banked and used in basic, translational and clinical research. This tissue is referred to as *residual* tissue, as compared to (extra) tissue *specifically* collected for scientific research. Significant medical progress has been made based on studies of tissue samples, especially in cancer research.e.g. 2,3

Consent for use of stored tissue for research purposes can be obtained in a variety of ways, and there is on-going discussion about which procedure complies best with patients' wishes while also being feasible in clinical practice. Some argue that implied consent with the opportunity to opt-out is sufficient. Under opt-out, information about research with tissue is provided but patients only need to inform their physician or hospital if they do not want their tissue to be used. Others claim that explicit one-time *general* (for all future research) consent should be asked.

Data about patients' preferences and wishes regarding information and consent procedures for tissue use are available primarily from trials in which tissue or blood was taken specifically for research purposes. Much less research on these issues has been carried out in hospital-based settings where *residual* tissue or blood obtained during diagnostics or treatment may be used for research. In addition, the research results that have been obtained have not been translated to clinical practice.

### Regulation of use of residual human materials in research

Two important laws regulating tissue use in the Netherlands are the Dutch Medical Treatment Act (WGBO) and the Medical Research Involving Human Subject Act (WMO). According to the Dutch Medical Treatment Act, anonymous samples obtained during medical treatment may be used in medical research if the patient has not objected to this secondary use. Active consent for use of such materials is not required and the law does not specify how patients should be informed about secondary use of tissue. The Medical Treatment Act does not regulate the use of coded samples. This is done by the 'Code of Conduct for proper secondary use of human tissue in research' published by the Dutch Federation of Biomedical Scientific Societies, together with the Royal Dutch Medical Association and several patient groups. According to this 'Code of Conduct', the use of *residual* tissue is regulated by an 'opt-out' procedure, as in many other countries. Patients can declare that they do not agree with the use of their tissue on the basis of information which in most hospitals is available in a general leaflet. In the future however, use of residual tissue might be regulated by the Human Tissue Act that the Dutch government has been working on for several years now.

Research with tissue *specifically* collected for research is regulated by the Medical Research Involving Human Subjects Act (WMO). This act states that respondents should always be asked written informed consent in this situation (<http://www.ccmo-online.nl/main.asp>).

During the formulation of the Medical Treatment Act it was debated whether it would be preferable to establish a procedure based on 'one-time general consent'. The report of the Royal Dutch Academy of Sciences (KNAW) on multifactorial diseases concluded that the

opt-out regime is preferable, largely based upon concerns that asking for one time general consent would not be feasible in the clinical setting and that therefore consent would not be obtained for a substantial proportion of patients. Moreover, there is empirical evidence that specific groups of patients would likely decline consent and that the tissues available for research would be biased.e.g. 17 Another problem related to obtaining consent via the one-time consent procedure is the burden for the hospital staff which may lead to missing forms. The Advisory Council on Health Research (RGO) supported the conclusion of KNAW and advised in 2007 to formulate the new Human Tissue Act based on Federa's Code of Conduct. However, some health lawyers state that patients should be able to give or withhold active consent. As such, proposed changes in Dutch regulation on the use of these samples, i.e. the obligation to obtain (one-time) informed consent from all 'donors' involved, may hamper future research. It has been argued that such an informed consent procedure will not be to the benefit of patients or researchers. Moreover, many patients do not believe informed consent is necessary.

A disadvantage of the current opt-out procedure, however, is that patients are generally not aware that tissue is stored for a future diagnosis. This is an important deficit when considering the importance of stored tissue for an eventual future diagnosis of the patient or her/his relatives. The fact that patients are not aware of tissue storage also signals the fact that most patients are not aware that they can opt-out (declare that they do not agree to the use of their extracted and stored tissue in medical research). In our exploratory research (see below) we therefore devised and tested a procedure that ensures that patients are aware of storage and research with residual tissue. This procedure, opt-out plus, involves verbal information and a leaflet about tissue research. With this information the patient can consider opting-out. In contrast to informed consent, the opt-out plus procedure does not require much administrative work because there is no need to process consent forms from all patients. Moreover, the opt-out plus procedure may not lead to lower consent rates and bias in the available tissue, as is very likely the case with the informed consent procedure, because this procedure does not depend on an action taken by patients.

## **Preliminary results**

Over the last years our research group has conducted three explorative studies about consent and patient information. We examined how patients in the NKI-AVL and VUmc with breast cancer, prostate cancer and colorectal cancer wished to be informed about research with stored tissue, and what kind of consent procedure they preferred. The studies showed that most respondents (96-98%) consented to research with their tissue. This is in line with other research. In the first study, patients were asked whether they preferred informed consent or opt-out. Most patients preferred a consent procedure with active information, but did not consider the signing of a consent form important, especially because they endorsed research and wanted to minimize bureaucratic burden. The respondents in these studies suggested a procedure that was labelled 'opt-out plus': patients receive verbal and written information, a special leaflet about tissue and research, and the option to opt-out.

In the two subsequent studies, the opinion of patients about the three consent procedures - informed consent, opt-out and opt-out plus- was explored by means of written questionnaires and telephone interviews. Further, the influence of these procedures on consent rates and availability of residual tissues for scientific research was studied. The majority of patients

preferred opt-out plus over the two other procedures. Opt-out and opt-out plus resulted in the highest availability of tissue for scientific research.

Previous studies thus indicate that opt-out plus is promising because it places few demands on administrative resources of the medical staff of hospitals while addressing the information needs of patients. These studies were, however, exploratory in nature and included small numbers of selected surgical cancer patients. In order to determine the best way of informing Dutch patients (with various diagnoses) the three consent procedures will be evaluated in this study in more diverse patient populations and different settings. The outcome of the current KWF-funded 4-year study will provide evidence on the patients', clinicians', and researchers' points of view that can be used in the current debate about new regulations regarding residual tissue use. The results may guide the implementation of a nationwide consent procedure and information leaflet for research with residual tissues. It is clearly in the interest of patients, clinicians and researchers to determine the most feasible, effective and acceptable way to gain consent from patients for the use of their residual tissue in medical research.

A more detailed overview of the background of this study and of the results of previous studies in our research group on consent procedures can be found in attachment A.

## **Study objectives**

The main part of this study aims to determine patient preferences for and satisfaction with consent procedures regarding the use of residual tissue for research, to provide insight into the type of information patients need to decide on the use of their material in research, and to determine the optimality of the timing and the content of these procedures in clinical practice. We will compare the three consent procedures, opt-out, opt-out plus and informed consent, with respect to the following primary study outcomes:

1. Patients' satisfaction with and preference for a consent procedure
2. Proportion of patients aware of storage of tissue and research use
3. Consent rates
4. Medical staff's satisfaction with and preference for a consent procedure

Additionally, we will obtain information on (1) the proportion of non-consent due to non-response; (2) the characteristics of non-consenters and non-respondents; and (3) the reasons for providing or withholding consent or (non-)response. We will investigate how patients perceived the information they received about residual tissue use and their knowledge about this topic. Patients' preferences to provide or withhold consent for specific types of research (e.g. genetic, commercial) and feedback regarding unanticipated findings will be investigated as well. Further, we will examine whether consent rates, satisfaction with or preference for a consent procedure differ according to severity of disease, type of clinical procedure (e.g., biopsies or surgical removal of tissue), diagnosis, type of hospital (academic or community) or demographics. Six months after the first questionnaire, we will examine whether patients are still aware of the decision they made and whether they are still satisfied with their choice to provide or withhold consent.

## **Hypotheses**

Hypotheses regarding the primary study outcomes are:

1. Patients' will be significantly more satisfied with the informed consent and opt-out plus consent procedures than with the opt-out consent procedure
2. Most patients will prefer the opt-out plus consent procedure, the lowest proportion of patients will prefer the opt-out consent procedure.
3. Significantly more patients will be aware of storage of tissue and research use in the informed consent and opt-out plus procedures than in the opt-out procedures.
4. Consent rates will be highest in opt-out and opt-out plus.
5. Members of the medical staff will be most satisfied with and prefer the opt-out and opt-out plus procedures.

## **Psychosocial measures**

Although some research has been conducted on the relation between specific psychosocial measures and patient preferences regarding information about their diseasee.g. 29 or regarding medical decision making,e.g. 30,31 to the best of our knowledge, no research has been conducted on the relation between such measures, such as patient satisfaction or coping style, and preferences for consent procedures for the use of residual tissues. Therefore, we add several psychosocial measures to our questionnaire. We consider this part of our study exploratory in nature.

This part of the study will investigate whether physical functioning, mental health, satisfaction with medical care, coping style and one's psychological reaction to stressful events influence a patient's preferences for and satisfaction with consent procedures. Moreover, we will investigate whether these variables influence consent rates.

## **Outcomes**

The primary study outcomes will be used to determine which consent procedure serves the needs of patients, clinicians and scientific research best. If one of the three consent procedures serves the needs of all three of these parties best, we will conclude that this consent procedure is the best candidate to become the standard procedure in the Netherlands that prescribes whether and how patients should be asked consent for the use of residual tissue. If the needs of these three parties are best served by different consent procedures, or if it is unclear which consent procedure serves the needs of one or more of the parties best, we will organize an invitational conference in which we invite different stakeholders, such as clinicians, patient organizations and researchers, to discuss how to translate our research findings into clinical practice.

Which consent procedure serves a party's needs best will be decided along the following lines:

- For patients: satisfaction with the received information in the 'best procedure' should be significantly higher than in the consent procedure with the lowest satisfaction rates. Further, the consent procedure should have the highest preference rates among respondents, with a minimum of a 10% difference with the consent procedure with the lowest preference rate. Additionally, the proportion of patients aware of storage of tissue and research use should be at least as high as in the other two groups.

- For clinicians: satisfaction with the received information in the ‘best procedure’ should be significantly higher than in the consent procedure with the lowest satisfaction rates. Further, the consent procedure should have the highest preference rates among participating clinicians and nurse practitioners, with a minimum of a 10% difference with the consent procedure with the lowest preference rate. Additionally, more than 75% of the responding medical staff should indicate that the consent procedure ‘never’ or ‘seldom’ interferes with giving clinical information.
- For research: consent rates for the procedure for which patients and/or clinicians have the highest preference should be at least as high as consent rates in the two other procedures.

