### **The intervention: 3 consent procedures**

Patients who receive the opt-out plus procedure (the patient is actively informed about the option to opt-out from research with residual tissue) and the informed consent procedure (the patient is asked for broad written consent for research with residual tissue) will receive specific information from their treating physician or a nurse practitioner by using a standardized text and a special information leaflet which is more extensive than the information leaflets currently available in the hospitals. In principle, this information will be given during a planned visit at the clinic. When this is impossible, the intervention might be conducted through telephone.

The consent procedures:

1. Opt-out plus. In this procedure patients will receive verbal and written information, and a specific leaflet (attachment F) on the use of residual tissue in research including an opt-out form. Patients can opt-out by returning this form using a stamped envelope.
2. Informed consent. In this procedure patients will receive verbal and written information and a specific leaflet (attachment G) on the use of residual tissue in research with a consent form to provide explicit written consent. Patients are asked to return the consent form using the

stamped envelope, indicating whether or not they consent to the use of their residual tissue in future research.

3. Opt-out (control). This group of patients will receive usual care. They may read information about the use of residual tissue in research in the (general) information leaflet of the hospital.

Patients in the two intervention arms will be informed by the medical staff using a standardized text (see below), which takes approximately one minute.

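### The rule for naming the best procedure tests satisfaction with the information received instead of the primary outcome, satisfaction with the consent procedure, and that measure is poorly comparable with the control arm

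*Protocol*

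**What the plan says.** The Outcomes section opens with "The primary study outcomes will be used to determine which consent procedure serves the needs of patients, clinicians and scientific research best". The first condition for patients then starts "For patients: satisfaction with the received information in the" best procedure, and this "should be significantly higher than in the consent procedure with the lowest satisfaction rates". The clinician condition uses the same wording.

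The Study objectives section gives primary outcome 1 as "Patients' satisfaction with and preference for a consent procedure", and primary outcome 4 is its counterpart for medical staff. Hypothesis 1 is that patients "will be significantly more satisfied with the informed consent and opt-out plus consent procedures than with the opt-out consent procedure".

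On the control arm, the summary's Methods section says "In the third arm, the control group, no (extra) information about residual tissue use is offered". The section on the three consent procedures adds "They may read information about the use of residual tissue in research in the (general) information leaflet of the hospital".

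**The concern.** The rule says it rests on the primary outcomes, but for satisfaction it uses another variable. Patients can be content with a leaflet and unhappy with how consent was handled, or the reverse.

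The substituted variable also depends on something the arms differ in by design. Both intervention arms get a specific leaflet and a standardized spoken text; the control arm gets neither. The rule does not say how a control patient who saw no information is counted.

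Because the satisfaction test is only against the lowest-scoring procedure, a control arm that scores low for lack of information could let both informed arms pass, whether or not patients are more satisfied with those consent procedures. The rule is meant to name a candidate national standard, so the choice of variable should be settled before results are known.

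**Working it through.** **Comparison of the text.** The plan states no figure for this criterion, so the first step is to set the sections side by side.

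| Protocol section | Object of satisfaction |
|---|---|
| Study objectives, primary outcomes 1 and 4 | consent procedure |
| Hypotheses, no. 1 | consent procedure |
| Sample size, statistical power (82% v 65%) | consent procedure |
| Basic plan of analysis, main arm comparison | consent procedure |
| Outcomes, patient and clinician conditions | information received |

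The description of the first questionnaire lists items on how the information was perceived separately from items on satisfaction with the procedure. These are two measures, not two names for one.

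**Inputs for the size of the effect.**
- Respondents per arm: 600 × 0.75 = 450 (sample size section).
- Two-sided alpha 0.05, as stated there for consent rates.
- Satisfaction rate 65%, used for illustration. It is the earlier opt-out plus rate for satisfaction with the procedure; no rate is given for the control procedure or for satisfaction with information.
- f, the share of control respondents who received any information. The protocol does not give it, so a range is shown.

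Power = Φ[(|p1 − p2| − 1.96·SE0)/SE1], where SE0 = √[p̄(1 − p̄)(1/n1 + 1/n2)], SE1 = √[p1(1 − p1)/n1 + p2(1 − p2)/n2] and p̄ is the pooled proportion.

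**Reading (a): only receivers are rated.** The control group has 450·f patients. The smallest difference from 65% detectable with 80% power is:

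| f | controls rated | detectable difference (points) |
|---|---|---|
| 100% | 450 | 8.6 |
| 50% | 225 | 10.4 |
| 25% | 112.5 | 13.0 |
| 10% | 45 | 18.1 |

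Precision falls. More importantly, those who read the leaflet chose to, so the comparison is no longer between randomized groups.

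**Reading (b): non-receivers count as not satisfied.** Let true satisfaction among receivers be 65% in both arms, so that there is no real difference. The control rate becomes 0.65·f. For f = 80%: 0.65 × 0.80 = 0.52, difference 0.13, p̄ = 0.585, SE0 = 0.0328, SE1 = 0.0326, and power = Φ[(0.13 − 1.96 × 0.0328)/0.0326] = Φ(2.02) ≈ 98%.

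| f | control rate | probability that an informed arm is significantly higher |
|---|---|---|
| 95% | 61.8% | 17% |
| 90% | 58.5% | 52% |
| 85% | 55.3% | 85% |
| 80% | 52.0% | 98% |
| 50% | 32.5% | about 100% |

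Under this scoring the condition is close to automatic once about 20% or more of controls received nothing.

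**With the primary outcome instead.** All 450 respondents per arm can be asked about the procedure. For the protocol's own 82% v 65%, the same formula gives power above 99.9%. Power against the control arm cannot be computed, because no control rate is given.

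**The case against.** The best defence is that this is loose drafting. The opening sentence names the primary outcomes, and the same phrase recurs for clinicians, where it fits poorly. The analysis plan also mentions satisfaction with the information when it describes analyses by patient characteristics, so the variable is not foreign to the study. That explains how the wording may have arisen, but the stated criterion still departs from the primary outcome.

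A third reading is open: every control patient rates whatever usual care provided, and a low score is then a genuine property of opt-out. This is fair. The questionnaire is an attachment that is not shown and may contain such an item. For that reason a reader might infer too much by calling the criterion undefined or automatic. Controls may read the general leaflet, and near-automatic passing needs both reading (b) and a sizeable share of non-receivers.

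A reader might also infer that the powered outcomes are left out of the decision. They are not. Consent rates and preference, which the sample size section calls the major outcomes, both enter the rule, as does awareness. Passing on satisfaction alone selects no procedure, and unclear results go to a stakeholder conference.

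Finally, a control patient unaware of any procedure is hardly better placed to rate the procedure than the information. This stands: changing the variable is not enough without a counting rule.

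**Conclusion.** The point holds in a limited form. The Outcomes section contradicts itself and the Study objectives on which satisfaction measure decides, in both the patient and the clinician conditions. For patients, the measure it names is poorly comparable between the informed arms and the control arm, and the rule leaves the counting of non-receivers open.

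The size depends on that counting. Rating receivers only gives a self-selected control group, with a detectable difference of 13.0 points instead of 8.6 if a quarter received information. Counting non-receivers as dissatisfied gives a false advantage with probability 52% at f = 90% and 98% at f = 80%. These figures rest on an assumed f, on a 65% rate borrowed from another measure and arm, and on 450 respondents per arm.

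The effect is confined to one of three joint patient conditions and to the satisfaction part of the clinician condition. The documents do not show that the whole decision would be wrong. All three patient conditions must hold, however, so a misdirected one can still change which procedure qualifies.

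**What to change.** In the Outcomes section, replace satisfaction with the information received by satisfaction with the consent procedure, in both the patient and the clinician conditions.

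For patients, add that:
- the same item is used in all three arms;
- all respondents are analysed;
- the way respondents unaware of any procedure are counted is fixed before results are seen.

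Report satisfaction with the information descriptively.

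The cost is a wording change and one pre-stated scoring rule. The first patient questionnaire already lists items on satisfaction with the procedure. For staff, the protocol text describes items on preference and on experience with the three procedures; check that the attached questionnaires, which are not shown, include a satisfaction item.
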